#### Effectiveness analyses

First, we will compare baseline characteristics of women participating in the intervention and control group using independent t-tests and chi-square tests. Second, we will compare baseline characteristics of drop-outs and completers by using independent t-tests and chi-square tests. Third, we will perform multiple logistic multilevel regression analysis to test the possible effect of routine third trimester ultrasound screening on severe adverse perinatal outcome. This analysis will be adjusted for possible clustering of observations at the level of midwifery practices and medical/biological, demographic and life-style related confounders. In all analyses, we will use an intention-to-treat approach and set the level of significance at *p* < 0.05.

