## Methods/design

### Study design

The IRIS study is a nationwide stepped wedge cluster-randomized trial among 15,000 low-risk pregnant women receiving care at 60 midwifery practices in the Netherlands. The intervention entails routine third trimester ultrasound screening combined with serial fundal height measurements and clinically indicated ultrasonography, while the control condition entails CAU (serial fundal height measurements and clinically indicated ultrasonography only). In 1500 pregnant women derived from the entire study population a survey will be conducted to assess societal costs, maternal psychological functioning, maternal quality of life, and infant neurodevelopment. The exact design of the survey will be described in more detail later on.

Two sub-studies will be conducted as part of the IRIS study. In sub-study A, a Delphi study will be conducted to develop a multidisciplinary consensus-based protocol for the detection and subsequent management of IUGR in the Netherlands. Sub-study B will address ethical considerations of additional/routine third trimester ultrasound screening. These sub-studies will be described in more detail later on.

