**Fig. 1 Fig1:**
[figure not shown]
Flow chart study design

During the first consultation after the 20-weeks pregnancy ultrasound screening has been offered, eligible pregnant women will be given a trial information leaflet by their midwife. The midwife will obtain consent.

Midwifery practices will form the unit of randomization. Randomization per practice rather than per midwife or woman minimizes contamination and maximizes contrast between the intervention and control group. As shown in Fig. 2, all midwifery practices (*n* = 60) will start in the control group. At 3 months intervals, a third of the midwifery practices will change status from the control to the intervention condition. To balance the number of women in the two conditions, practices will be stratified before randomization in large and small practices, with the average practice size as cut‐off (250 women per year). A stratified computer‐generated random sequence will determine the order in which practices change from control to intervention status. Randomization will be conducted by an independent statistician at 3 and 6 months after the start of baseline data collection and the recruitment of the first participating women.

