### Measures

#### Baseline characteristics of pregnant women and midwifery practices

To assess comparability of study groups and predictors of outcome, data on baseline characteristics of participating midwifery practices and participating pregnant women will be collected. Baseline characteristics of midwifery practices will include number of midwives working in the practice, number of clients per year, proportion of nulliparous and multiparous women, and rate of referral to secondary/tertiary care. Maternal baseline characteristics will include ethnic background, maternal age, educational level, height and weight, smoking, alcohol use, drug use, and work status during pregnancy.

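### The woman-level t-tests and chi-square tests planned for baseline comparability ignore practice randomisation and calendar time, so they reject more often than 5% by an amount that depends on ICCs the protocol does not give (minor)

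*Protocol article*

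**What the plan says.** The section on baseline characteristics of women and practices gives the purpose of these data: "To assess comparability of study groups and predictors of outcome, data on baseline characteristics" will be collected. It lists what is recorded for the women: "Maternal baseline characteristics will include ethnic background, maternal age, educational level, height and weight, smoking, alcohol use, drug use, and work status during pregnancy".

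The Effectiveness analyses section then names the method: "we will compare baseline characteristics of women participating in the intervention and control group using independent t-tests and chi-square tests". The closing sentence of that section covers all analyses and will "set the level of significance at *p* < 0.05". Practice clustering appears only in the third step, the multilevel logistic model for the primary outcome: "This analysis will be adjusted for possible clustering of observations at the level of midwifery practices".

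On the design, the Recruitment and randomization section says "Midwifery practices will form the unit of randomization" and "At 3 months intervals, a third of the midwifery practices will change status from the control to the intervention condition". The caption to Fig. 2 places enrolment in months 1 to 12. The sample size section accepts that the clustered design means dependency between observations has to be allowed for.

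**The concern.** An independent t-test or a chi-square test derives its standard error from independent women. That would be right if women had been allocated one by one, or if practices did not differ in case-mix. Here practices are allocated to switching dates. Early switchers contribute mostly intervention women and late switchers mostly control women. Ordinary differences between practices in, say, ethnic background or smoking therefore enter the crude contrast, and the test's standard error does not include them.

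Calendar time is also ignored. All practices start in control and move one way, so the two groups are enrolled at different times on average. Any seasonal or secular change in who is enrolled appears as a difference between conditions.

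What is at stake is how the comparability table is read. A significant result could reflect a change in enrolment after the switch, normal variation between practices, or time, and the planned tests cannot tell these apart. The midwife informs women and obtains consent while the practice is in a given condition, so a change in enrolment at the switch is a reasonable thing to want to see clearly.

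**Working it through.** **Inputs from the protocol article.** 60 practices and 15,000 women (Study design); 7,500 women per condition (Abstract); average cluster size 250 (sample size section); a third of practices switching at 3-month intervals (Recruitment and randomization); 12 months of enrolment (Fig. 2 caption); 5% level (Effectiveness analyses).

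**Assumptions.** Two-sided tests; even enrolment; switches at 3, 6 and 9 months in three sequences of 20 practices; a practice effect constant over time; no time trend; and a range of ICCs for baseline characteristics, since none is given.

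**The plan's own figures.** The article gives no error rate for the baseline tests. Its sample size arithmetic does reproduce. The standard two-proportion formula for 1.54% against 1.0% with 80% power gives 13,498, close to the stated 13,536. The clustering correction gives 13,536 x (1 + 249 x 0.0003) = 13,536 x 1.0747 = 14,547, as stated.

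**Shares by practice.** Control-to-intervention months are 3:9, 6:6 and 9:3 in the three sequences. For a practice of 250 women these are 62.5:187.5, 125:125 and 187.5:62.5. The difference is 125 women in absolute size for 40 practices and zero for 20.

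**Variance of the crude difference** (outcome variance 1):

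ICC x sum over practices of (n_int/7,500 - n_ctl/7,500)^2 + (1 - ICC) x (2/7,500)

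The sum is 40 x (125/7,500)^2 = 0.01111, and 2/7,500 = 0.000267. The ratio of the two is 41.67. Relative to what the test assumes, the inflation is (1 - ICC) + 41.67 x ICC = 1 + 40.67 x ICC.

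**True rejection rate** of a nominal 5% test: 2 x (1 - Phi(1.96 / sqrt(inflation))).

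| ICC | Inflation | True rejection rate |
|---|---|---|
| 0.0003 (article, neonatal mortality) | 1.01 | 5.1% |
| 0.002 (article, neonatal mortality) | 1.08 | 5.9% |
| 0.01 (assumed) | 1.41 | 9.8% |
| 0.02 (assumed) | 1.81 | 14.6% |
| 0.05 (assumed) | 3.03 | 26.0% |
| 0.10 (assumed) | 5.07 | 38.4% |

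**Simulation check.** With 4,000 trials per setting and equal practice sizes, the rates for a continuous characteristic were 9.6%, 14.6%, 26.1% and 37.9% at ICCs of 0.01, 0.02, 0.05 and 0.10. With an assumed coefficient of variation of 0.5 in practice size they were about 11%, 16%, 31% and 43%. A binary characteristic with 20% prevalence behaved similarly. In a separate simulation of 2,000 trials per ICC, a comparison with practice and quarter effects rejected in 4.4% to 5.5%.

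**Calendar time.** In successive quarters, 60, 40, 20 and 0 practices are in control and 0, 20, 40 and 60 in intervention. With quarter midpoints of 1.5, 4.5, 7.5 and 10.5 months, mean enrolment time is (60 x 1.5 + 40 x 4.5 + 20 x 7.5)/120 = 3.5 months in control and (20 x 4.5 + 40 x 7.5 + 60 x 10.5)/120 = 8.5 months in intervention. The gap is 5 months. The rejection rates above assume no time trend, so they do not include its effect.

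**The case against.** The strongest objection is about size. The only ICCs in the article are 0.0003 to 0.002, and at those values the tests are almost correct. This stands in part: a large excess rests on assumed values, and a reader who infers that the tests will reject far above 5% whatever the clustering goes beyond the document. But those ICCs are for neonatal mortality, and the article itself links low ICCs to low prevalence. They are not evidence that education, ethnic background or smoking cluster as little. The direction is certain for any ICC above zero; only the size is open.

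The second objection is that nothing depends on these p-values. The primary model adjusts for practice and for named groups of confounders, and the article does not say that baseline tests select those confounders. This stands. A reader might infer that the primary estimate is compromised, but the text does not support that.

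Third, a significant baseline result would not be imaginary. If practices with different case-mix contribute unequally, the pooled women really do differ by chance. This also stands. The test overstates the evidence for a systematic difference and cannot identify the source, but it does not invent the difference.

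Other stronger readings also fail:

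- A parallel-cluster formula would give 59% at an ICC of 0.05, but it does not fit a design in which every practice supplies both conditions.
- A combined chance of at least one significant characteristic would need a common ICC and independent characteristics, and neither is supported.
- The baseline table is not assigned the role of detecting differential enrolment. The process measures separately record how many women decline.
- The drop-out comparison uses the same tests, but no error rate has been worked out for it, so it is not part of this point.

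Finally, one might say that a condensed article leaves such detail to the analysis plan. Here the article names the tests, so this is a stated choice and not an omission.

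**Conclusion.** The point holds in a limited form. The named tests do not match the randomisation, and they reject more often than 5% when there is no systematic difference between conditions. The rate is about 10% at an ICC of 0.01, 26% at 0.05 and 38% at 0.10, somewhat higher with unequal practice sizes, and near nominal at the article's outcome ICCs. These figures rest on assumed baseline ICCs, two-sided tests, even enrolment, steps at 3, 6 and 9 months, and no time trend. The effect is confined to the comparability assessment; the primary effect estimate and its test are not touched. Severity: minor.

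**What to change.** In the Effectiveness analyses section, remove the independent t-tests and chi-square tests for the intervention-control comparison. Present baseline characteristics by condition descriptively, for example with standardised differences. This also avoids drawing attention to trivial gaps: with 7,500 women per condition, the planned test calls a difference of 1.96 x sqrt(2/7,500) = 0.032 standard deviations significant.

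If a test for differential enrolment is wanted, fit each characteristic as the outcome in a multilevel linear or logistic model with practice and enrolment quarter, and report the condition coefficient with its 95% confidence interval.

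This changes analysis wording only. It uses data already to be collected and the kind of model already planned for the primary outcome. The cost is slightly more programming and wider intervals for the baseline differences.

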Moreover, additional third trimester ultrasonography may affect maternal emotions, either positively in that negative screening results may be reassuring, or negatively in that it may increase maternal emotional distress, i.e., anxiety or depressive symptoms. Women may experience higher levels of emotional distress, due to an (incorrect) indication of IUGR and be exposed to additional monitoring and obstetric interventions [18, 19]. Experiences of maternal emotional distress due to positive, unexpected or unclear findings based on fetal ultrasound screening may continue into the postpartum period, even when abnormal screening results have not been confirmed by subsequent examinations [20–22].

In the case of positive screening results routine third trimester ultrasonography may particularly be related to the experience of moral dilemmas by pregnant women and professionals performing ultrasonography. For example, parents may find this burdensome due to increased responsibility that comes with the fact that they have to choose for further examinations of the fetus (or not). Professionals may find it difficult how to decide how much and which information they should provide to women/parents and when to advice referral for further clinical management [20–23].

Despite the lack of evidence for its clinical effectiveness [14, 15], routine third trimester ultrasound screening is increasingly used in midwifery care in the Netherlands, which results in a considerable rise in health care costs. Few former studies evaluated the cost-effectiveness of ultrasound scans [24, 25]. Although costs of the ultrasound examination itself have previously been investigated, we know little about resulting costs (e.g., costs associated with subsequent counselling, follow-up examinations, and subsequent interventions). So far, only one previous trial, The Helsinki ultrasound trial, addressed this matter showing that one-stage second-trimester ultrasound screening is cost-effective in reducing perinatal mortality as compared to care as usual when taking all significant costs and effects into account [25]. Moreover, the cost-effectiveness of routine third-trimester ultrasound screening combined with serial fundal height measurements and clinically indicated ultrasonography as compared to care as usual (CAU), i.e. serial fundal height measurements and clinically indicated ultrasonography alone, has not been studied earlier.

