**Fig. 2 Fig2:**
[figure not shown]
The stepped wedge design of the IRIS study. Pregnant women will be enrolled during months 1–12 at 20–22 weeks of gestation. All midwifery practices (*n* = 60) will start with the control condition providing care as usual. At intervals of 3 months, a third of all practices will change status from the control to the intervention condition, which means providing routine third trimester ultrasound screening at 28–30 weeks and 34–36 weeks of gestation. Postnatal follow-up will be conducted in months 18–42

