### Care in the intervention and control group

Both the intervention group and the control group will receive the following standard elements of midwifery care: 1) serial fundal height measurements and clinically indicated ultrasonography in line with the KNOV guideline for the detection of IUGR [26]; 2) information about life-style factors that may influence fetal development, e.g., smoking and alcohol use; and 3) advice to report a reduction in fetal movements. When IUGR is suspected, both groups will receive subsequent management based on the consensus-based protocol that will be developed in sub-study A.

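### The stated primary model of this stepped wedge trial has no calendar-period term, so part of any secular trend enters the estimated effect of screening

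*Protocol article*

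**What the plan says.** The Study design section describes a stepped wedge trial with 60 practices as clusters and 15,000 women. Under Recruitment and randomization every practice begins under control, and the switching rule reads: "At 3 months intervals, a third of the midwifery practices will change status from the control to the intervention condition". The Fig. 2 caption gives the enrolment window: "Pregnant women will be enrolled during months 1–12 at 20–22 weeks of gestation".

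The primary analysis is under Effectiveness analyses: "we will perform multiple logistic multilevel regression analysis to test the possible effect of routine third trimester ultrasound screening on severe adverse perinatal outcome". The article then lists what this model adjusts for: "This analysis will be adjusted for possible clustering of observations at the level of midwifery practices and medical/biological, demographic", with life-style factors as the last item. No calendar period, step or other time term appears there or elsewhere in the article. The sample size section inflates an individually randomized sample by the parallel-cluster factor 1 + (n − 1) × ICC, which also makes no allowance for period.

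**The concern.** In a stepped wedge trial, randomization fixes only the order in which practices switch. Every practice moves from control to intervention as time passes, so condition and calendar time are associated by design. The one confounder that the design itself creates is absent from the stated adjustment. A practice random intercept does not remove it, because all practices move through time in the same direction. Maternal characteristics do not measure time.

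The article gives grounds for not assuming a flat background. It says that "routine third trimester ultrasound screening is increasingly used in midwifery care in the Netherlands". It also introduces a newly developed management protocol under which, when growth restriction is suspected, "both groups will receive subsequent management based on the" consensus document. If uptake of either changes over the enrolment year and affects outcomes, the change falls unequally on the two conditions. A falling background risk would look like benefit of screening. A rising one would hide benefit or look like harm.

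**Working it through.** **Inputs from the protocol article.** 60 practices; three groups of 20 switching at 3-month intervals; enrolment in months 1–12 (four quarters); 15,000 women; 1.54% versus 1.0%; 80% power; significance level 0.05; cluster size 250; ICC range 0.0003 to 0.002.

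**Assumptions.** Equal practice sizes and even recruitment (62.5 women per practice per quarter); a linear approximation on the risk scale; two-sided testing.

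**1. The plan's own figure.** Two proportions, 1.54% versus 1.0%, two-sided 0.05, 80% power, no continuity correction: 13,498 women in total, against 13,536 stated. Clustering: 13,536 × (1 + 249 × 0.0003) = 14,547, as stated. The published sample size is therefore that of a parallel design without period effects.

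**2. How far condition follows time.** Numbers of practices by quarter: control 60, 40, 20, 0; intervention 0, 20, 40, 60.

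- Mean quarter, control: (1×60 + 2×40 + 3×20)/120 = 1.67.
- Mean quarter, intervention: (2×20 + 3×40 + 4×60)/120 = 3.33.
- Gap: 1.67 quarters = 5 months.
- Quarters 1 and 4 have one condition only: 2 × 3,750 = 7,500 of 15,000 women.
- Variance of condition explained by quarter: [(0.5² + 0.167² + 0.167² + 0.5²)/4]/0.25 = 0.139/0.25 = 0.556 (correlation 0.75).

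**3. Bias without a period term.** With a linear trend of b points per quarter and ICC near 0, the bias is 1.67b. The first-to-last-quarter change is 3b, so the fraction carried over is 1.67/3 = 56%. Generalized least squares with a practice random intercept at ICC 0.0003 also gives 56%, and at ICC 0.002 it gives 59%. The random intercept does not help.

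**4. Type I error.** There is no true effect, ICC is 0.0003, and the variance is taken at the mean risk over the four quarters. The error is Φ(−1.96 − z) + 1 − Φ(1.96 − z), with z = bias/SE. The trends are assumed; the documents give none.

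| Fall per quarter (points) | Risk in last quarter | False reduction (points) | Share of 0.54-point target | SE (points) | Type I error |
|---|---|---|---|---|---|
| 0.026 | 1.46% | 0.044 | 8% | 0.200 | 5.6% |
| 0.05 | 1.39% | 0.084 | 16% | 0.197 | 7% |
| 0.10 | 1.24% | 0.169 | 31% | 0.192 | 14% |
| 0.15 | 1.09% | 0.253 | 47% | 0.187 | 27% |

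These falls are about 5%, 10%, 19% and 29% of 1.54% over the year. With categorical period effects the bias is zero and the error is 5% in every row. At ICC 0 or 0.002 the type I errors change by about 1 percentage point or less.

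**5. Price of adjusting.** At ICC 0 the standard error rises by 1/√(1 − 0.556) = 1.5. For planning, with mean risk 1.27% and ICC 0.0003, it goes from 0.184 to 0.278 points.

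- Power without period: Φ(0.54/0.184 − 1.96) ≈ 84%.
- Power with period: Φ(0.54/0.278 − 1.96) ≈ 49% (50% at ICC 0; 45% at ICC 0.002).
- Women needed for 80% power with period: about 32,000 at ICC 0.0003, against about 13,600 without.

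**The case against.** The best defence is that this is a condensed journal article, and that the analysis plan, which is not shown, may include a period term. The article names broad classes of covariates, not a model formula. This limits the claim: nobody can conclude from the article that the trial will be analysed without period. It does not dispose of the point. The article does state what the primary model adjusts for, and its sample size matches an analysis without period effects. A reader following the text as written would fit the biased model.

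Several stronger readings are tempting, and the documents do not support them:

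- *All of any trend is counted as effect.* Only about 56% of a linear first-to-last-quarter change is carried over.
- *The comparison is essentially before-after.* Half of the women enrol in quarters 2 and 3, where both conditions run side by side.
- *Type I error will be 14% to 27%.* Those figures belong to falls of 19% and 29% within one year, which nothing in the article supports. With a 5% fall the error is barely above nominal, and with no trend it is nominal.
- *A trend is established.* Rising national use of scans is not a trend in severe perinatal outcome. A protocol applied to both groups from the start would shift the level; only gradual uptake would produce a trend. Practices must be willing to have their midwives trained, but no text says that training begins everywhere at trial start.
- *Leaving the practice-size stratum out of the model is also an error.* Every practice contributes to both conditions and practice is already modelled. No effect of leaving the stratum out has been shown.

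**Conclusion.** The point holds as a defect in the stated primary model. The stepped wedge schedule makes condition depend on calendar time, and the stated adjustment omits it. The exposure to bias is structural; its size depends on a trend that the documents do not give. Over the assumed range the false reduction is 8% to 47% of the target effect, and type I error runs from about 5.6% to 27%. A rising trend would bias the estimate in the opposite direction. The figures rest on even recruitment, equal practice sizes, linear trends and a linear approximation for a rare binary outcome, so they are approximate. The choice of model has to be settled before outcomes are seen, because the two models differ by a factor of 1.5 in standard error and a later choice between them would be open to bias.

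**What to change.** State that the primary model is a multilevel logistic regression with condition, categorical enrolment period (four 3-month periods) as a fixed effect, practice as a random effect, and the planned maternal covariates. Name the period-adjusted effect as the primary result. Use the same period term in any secondary outcome model that follows this approach. Adding the practice-size stratum is optional.

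In the text this is one sentence, and it requires each woman's enrolment period in the analysis file. The real cost is precision. The power statement under Sample size of the trial must be recalculated for the stepped wedge design with period effects, and either the sample size or the claim of adequate power in the Discussion revised accordingly.
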